## Abstract

Subjects affected by schizophrenia present significant deficits in various aspects of social cognition, such as emotion processing, social perception and theory of mind (ToM). These deficits have a greater impact than symptoms on occupational and social functioning. Therefore, social cognition represents an important therapeutic target in people with schizophrenia. Recent meta-analyses showed that social cognition training (SCT) is effective in improving social cognition in subjects with schizophrenia; however, real-life functioning is not always ameliorated. Integration of SCT with an intervention targeting metacognitive abilities might improve the integration of social cognitive skills to daily life functioning. Our research group has implemented a new individualized rehabilitation program: the Social Cognition Individualized Activities Lab, SoCIAL, which integrates SCT with a module for narrative enhancement, an intervention targeting metacognitive abilities. The present multi-center randomized controlled study will compare the efficacy of SoCIAL and treatment as usual (TAU) in subjects diagnosed with a schizophrenia-spectrum disorder. The primary outcome will be the improvement of social cognition and real-life functioning; while the secondary outcome will be the improvement of symptoms, functional capacity and neurocognition. The results of this study will add empirical evidence to the benefits and feasibility of SCT and narrative enhancement in people with schizophrenia-spectrum disorders.

## Introduction

In subjects with schizophrenia an impairment in different cognitive domains has been well established (1–9). Cognitive impairment has been associated with poor social functioning and poor quality of life (10–14). Evidence has been reported suggesting that the impact of cognitive impairment in real-life functioning is even greater than the one exerted by positive and negative symptoms (15–19). Furthermore, this impairment can be detected throughout different phases of schizophrenia, such as the premorbid, prodromal and remission stages of the illness (20–25). From a neurobiological perspective, this impairment might be explained as the cumulative effect of abnormalities in neuronal maturation processes, neurodevelopment and neuroplasticity that could lead to defective cortico-cerebellar-thalamic-cortical circuits (26–29).

Social Cognition (SC) is a complex construct that underlies fundamental abilities for social interactions, such as the capacity to perceive, interpret and generate answers based on other people’s intentions, emotions, and behaviors (4, 30–32). The ability to form integrated ideas about oneself, others, and the world based on SC, i.e., metacognition, is essential for the integration of the social cognitive skills to daily life functioning. Both SC and metacognition concur to construct a coherent narrative on internal experiences and behavior in different interpersonal situations (30, 31, 33).

Among all the cognitive domains, SC was highlighted not only for its direct impact on real-life functioning, but also for its role in mediating the effects of other cognitive domains on functioning (15, 17, 34, 35).

Studies regarding SC in schizophrenia identified 4 sub-domains impaired in affected subjects: emotion recognition, social role perception, theory of mind (ToM) and attributional style (30, 31, 36).

Despite the key role that cognitive impairment plays in schizophrenia, pharmacological treatments seem to have a marginal impact (2, 37, 38); consequently, a number of psychological treatments has been developed in order to get a significant improvement of several cognitive domains, quality of life and real-life functioning (39–46). Specifically, the cognitive remediation programs were developed mainly to target neurocognitive functions (such as attention, memory, learning) rather than SC, which only in the last decade became the target of specific training programs with promising results (30, 47–49).

Different approaches have been used to develop cognitive remediation programs for SC: some of them, defined as “integrated,” aimed to train both SC and neurocognitive domains; other programs, defined as “targeted,” are designed to improve only specific SC domains (50–53). A meta-analysis of SC programs showed that these interventions produce significant improvements in emotion recognition and ToM, as well as in real life functioning and in negative symptoms (49). According to the results of a recent meta-analysis, the inclusion of a training for neurocognition does not add any advantage (53). Furthermore, the meta-analysis also showed that generalization to real-life functioning of the improvement is not always obtained.

None of the social cognition training (SCT) programs included a focus on metacognition, specifically oriented to mediate and facilitate the transfer of therapeutic gains to real-life tasks.

The Department of Psychiatry of the University of Campania “Luigi Vanvitelli” developed an integrated group intervention, the Social Cognition Individualized Activities Lab (SoCIAL), with the purpose to improve SC domains (recognition of emotions and ToM). In the pivotal study, SoCIAL was compared to a largely validated remediation program for social abilities, the Social Skills and Neurocognitive Individualized Training (54–56). Results showed that participants who received the SoCIAL program improved their SC abilities, together with a significant reduction of the avolition domain in negative symptomatology, compared to the control group (56).

Conversely, no difference was found among the two treatment groups when looking at other clinical variables, such as positive and disorganized symptoms, neurocognitive functions and real-life functioning. In particular, both groups did not show an improvement in social functioning, probably due to a ceiling effect, i.e., the high level of functioning that these patients already had before the treatment started (56).

The main limitations found for this program concerned two aspects: (1) the group setting and (2) the role-play module. The group setting was not accepted by all subjects and participants’ recruitment was challenging as some subjects refused or were unable to attend the group sessions. The role-play, a very useful technique for the development of social abilities, is less effective in training SC, as subjects with greater SC deficits in the group may experience frustration during the role-play if other subjects present milder levels of SC deficits. The individual format of the SoCIAL training was found to be accepted by all subjects and allowed a better personalization of the SC training.

Additionally, to favor the transfer of therapeutic gain to real-life functioning we added an intervention on metacognition, focused on understanding the role of emotions and intentional states in real-life situations, to develop a coherent narrative about self and others. The literature has recently identified an interesting technique that could help individuals affected by schizophrenia train their narrative ability, i.e., *narrative enhancement* (57–63). Several studies have shown a correlation between narrative abilities and metacognition, i.e., the ability to integrate newly acquired cognitive skills to daily life functioning (64–66). Narrative deficits play a substantial role in determining the poor quality of life for people with schizophrenia and are associated with negative and depressive symptoms (65, 67). Some studies (57, 58) used the *narrative enhancement* technique in a rehabilitation program defined as “integrated,” since it trained both neurocognitive and narrative abilities. The results are encouraging, considering that this technique seems to considerably decrease internalized stigma and to improve quality of life of participants, even when compared to other psychological and rehabilitative programs (58).

The present protocol aims to evaluate the efficacy of the integrated SoCIAL program in a large sample of individuals with schizophrenia-spectrum disorders. The program will be administered individually and will include the *narrative enhancement* module, specifically developed to target metacognitive abilities to recognize and integrate mental states, such as emotions, desires, attitudes and goals in real-life situations. The efficacy of the program will be evaluated by comparing the participants randomized to SoCIAL with those randomized to treatment as usual (TAU). The use of the TAU control was deemed appropriate as the study is an early phase trial in which an active control condition including different treatment components may reduce power and increase type II error (68).

The study aims to compare the efficacy of the SoCIAL program vs. TAU in subjects with schizophrenia or schizoaffective disorder (based on DSM-5 criteria) with illness durations < 10 years. The primary outcome is the improvement of social cognition and real-life functioning; while the secondary outcome is the improvement of negative symptoms, functional capacity and neurocognition.

## Materials and Methods

### Subjects

The study will be carried out at the Department of Psychiatry of the University of Campania “Luigi Vanvitelli” in Naples, and the Department of Mental Health and Addiction Services, ASST Fatebenefratelli Sacco in Milan. Eighty consecutive outpatients with a diagnosis of schizophrenia/schizoaffective disorder according to DSM-5 criteria, confirmed by the Structured Clinical Interview for DSM-5-Patient version (SCID-I-P) will be enrolled, 40 in each center.

Inclusion criteria are: (1) age between 18 and 50 years; (2) clinical stability defined as no major pharmacological treatment modifications in the last 3 months; (3) illness duration < 10 years; (4) at least 5 years of school education. Exclusion criteria are: (1) medical conditions that cause disabilities; (2) a history of alcohol and/or substance abuse.

Subjects will be considered “drop out” when: (1) they do not participate in the study sessions for 3 consecutive weeks, or withdraw the consent to continue the study; (2) they do not participate in the study sessions for 3 consecutive weeks, re-join the program and then accumulate 2 more weeks of absence from the study (in total 5-week interruption of the program, even when non-consecutive); (3) worsening in psychopathological condition requiring a substantial modification of the pharmacological therapy and/or a hospitalization.

Subjects will be randomly assigned to the SoCIAL or the TAU group. Overall, 40 patients (20 for each center) will be assigned to SoCIAL and 40 (20 for each center) to the TAU. Subjects will be evaluated before starting the program and at the end of the intervention.

The study will be approved by the Ethics Committees of the two centers. All enrolled subjects will sign an informed consent form, approved by the Ethics Committees.

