### Data Analysis

An assessment of the statistical power of this study was performed using an effect size analysis of the studies included in a meta-analysis (49). The results are very satisfactory: with a statistical power ≥ 0.8 and a significance level of < 0.05, our study needs a total sample of 68 subjects largely below the 80 subjects that will be recruited.

Neuropsychological, psychopathological and cognitive functioning evaluations will be conducted pre and post interventions. Statistical analysis will be conducted by ANOVA for repeated measures, focusing on the role played by different types of interventions in each group regarding the aforementioned domains.

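### The drop-out rules fall unevenly on the two arms and depend partly on outcome, so the comparison is at risk of bias unless drop-outs are still assessed and analysed as randomised

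*Protocol article*

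**What the plan says.** The Subjects section gives three routes to drop-out status and names no arm in any of them.

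- Rule 1: "they do not participate in the study sessions for 3 consecutive weeks, or withdraw the consent to continue the study".
- Rule 2: "they do not participate in the study sessions for 3 consecutive weeks, re-join the program and then accumulate 2 more weeks of absence", which the text sums to a five-week interruption.
- Rule 3: "worsening in psychopathological condition requiring a substantial modification of the pharmacological therapy and/or a hospitalization".

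The SoCIAL programme section sets one session a week for 10 weeks. The Treatment as Usual section describes continuation of existing care and no study sessions. Assessments are at baseline and at the end of the intervention only (Subjects; Length of the Study; Table 1). Data Analysis states: "Statistical analysis will be conducted by ANOVA for repeated measures". The Introduction says that efficacy will be judged by comparing patients according to the arm to which they were randomised. Data Analysis also says "our study needs a total sample of 68 subjects largely below the 80 subjects that will be recruited". No expected drop-out rate is given for either arm.

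**The concern.** Being absent from study sessions requires having sessions to attend. A TAU patient can become a drop-out only by withdrawing consent or by worsening. A SoCIAL patient can also become one through poor attendance. Status assigned after randomisation therefore depends on the arm.

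Rule 3 applies to both arms, but it is triggered by a clinical course that the trial also measures: symptoms are a secondary outcome.

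Neither feature would do harm if every drop-out were still assessed and kept in the analysis. The article does not say that they are, because one term covers both leaving the programme and leaving the study. There is a single post-baseline measurement, so a patient not seen then has no outcome at all. A later analysis plan can model such a gap but cannot recover the value.

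Separately, rules 1 and 2 do not fit together. A patient absent for three consecutive weeks is already a drop-out under rule 1, yet rule 2 describes the same patient returning and being counted only after two more missed weeks.

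**Working it through.** **The plan's own figure.** The article gives 68 patients for power of at least 0.8 at a 0.05 level, but no effect size, so 68 can be neither confirmed nor refuted. Solved backwards with 34 per arm, two-sided (the article does not state sidedness):

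d = (1.960 + 0.842) × √(2/34) = 0.68 (normal approximation); 0.69 by the t distribution; 0.60 if one-sided.

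The margin between 80 and 68 is 12/80 = 15%.

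**Model for the attendance rules.** With two time points, the group-by-time test in a repeated-measures ANOVA is equivalent to a t-test on change scores. Take change with SD 1, no true effect and 40 per arm. Remove the fraction f of SoCIAL patients with the lowest attendance propensity, where that propensity correlates ρ with change. TAU loses nobody by this route. The bias is

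ρ × φ(z_f) / (1 − f),

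where z_f is the f-quantile of the standard normal and φ its density. At f = 0.15, φ(z_f)/(1 − f) = 0.274, so the bias is 0.3 × 0.274 = 0.082 or 0.5 × 0.274 = 0.137. Both f and ρ are assumptions; the article gives neither. Type I error comes from 20,000 simulated trials per setting, whose mean biases agree with the formula to within 0.003 SD.

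| Removed from SoCIAL | Bias, ρ = 0.3 (SD) | Type I error | Bias, ρ = 0.5 (SD) | Type I error |
|---|---|---|---|---|
| 10% | 0.058 | 5.8% | 0.097 | 7.0% |
| 15% | 0.082 | 6.1% | 0.137 | 9.0% |
| 20% | 0.105 | 7.1% | 0.175 | 11.0% |
| 30% | 0.149 | 9.3% | 0.248 | 16.7% |

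At ρ = 0 the bias is zero and type I error about 5%. At ρ = −0.3 the bias is −0.06 to −0.15 SD, against SoCIAL. If the implied effect of 0.69 is on the same scale, 0.06 to 0.25 SD is 0.06/0.69 = 9% to 0.25/0.69 = 36% of it.

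**Worsening rule, both arms, ρ = 0.5 (assumed).** The bias is the SoCIAL term minus the TAU term. φ(z_f)/(1 − f) is 0.195 at 10% and 0.350 at 20%.

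- 10% in each arm: 0.
- 10% SoCIAL, 20% TAU: 0.5 × (0.195 − 0.350) = −0.08 SD, against SoCIAL.
- 20% SoCIAL, 10% TAU: +0.08 SD, toward SoCIAL.

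**Both rules together** (20% attendance loss in SoCIAL at ρ = 0.3, worsening at ρ = 0.5, simulated): +0.09 SD when 10% worsen in each arm; +0.02 SD when 10% worsen in SoCIAL and 20% in TAU.

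**Power at d = 0.69 (t-test).** 40 vs 40 analysed: 0.86. 32 vs 40: 0.82. 32 vs 36: 0.80. 28 vs 36: 0.77.

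**The case against.** A reader might infer that a declared drop-out leaves the analysis. The article never says so. It says only how such patients are classed. The same section states without exception that subjects are evaluated before and after, and the Introduction describes an as-randomised comparison. A drop-out who attends the final assessment has both scores and stays in the ANOVA. This stands, and it makes the concern conditional on drop-outs not being assessed.

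A reader might also infer that the comparison is biased toward SoCIAL as a matter of fact, with the worsening rule adding to the bias. The documents do not support either. The attendance effect needs poor attenders to have worse change, not merely worse baseline severity, which the pre/post contrast largely removes. Patients are selected for clinical stability, and the Introduction reports that the individual format was accepted by all subjects, so both the correlation and the loss could be small. The worsening rule gives no net bias at equal rates and partly offsets the attendance effect if TAU patients worsen more often. Consent withdrawal under rule 1 applies to both arms.

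Analysis sets and missing-data methods are commonly left to a full protocol or analysis plan, so their absence here is no fault. That does not settle the matter. The drop-out rules are fixed in this text, and whether a post score exists is decided when data are collected, before any analysis plan is applied.

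**Conclusion.** The point holds as a conditional risk. The rules are asymmetric, because attendance can count only in SoCIAL, and partly outcome-related through worsening in either arm. If drop-outs are not assessed and analysed as randomised, the attendance rules plausibly favour SoCIAL by about 0.06–0.25 SD, with two-sided type I error of about 6–17%. This rests on assumed losses of 10–30% and an assumed attendance–change correlation of 0.3–0.5; the sign depends on that correlation. For the worsening rule the direction is undetermined: about zero at equal rates and roughly 0.08 SD either way at 10% against 20%. The conflict between rules 1 and 2 needs no assumption. This should be fixed as a cheap improvement; confidence is medium, because exclusion of drop-outs is a possibility left open and not a stated plan.

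**What to change.** 1. Word the three rules as definitions of discontinuing, or not adhering to, the programme, and state that meeting one does not end participation in the trial. Record consent withdrawal separately.
2. Carry out the already planned post assessment in every randomised patient who has not withdrawn consent, at the same time point in both arms.
3. Make the primary analysis all randomised patients in their allocated arm, with a method that keeps those lacking a post score, such as a likelihood-based repeated-measures model or multiple imputation.
4. Use the rules only to define a per-protocol sensitivity set, reported with the number meeting each rule by arm.
5. Reconcile rules 1 and 2 so that the status of a patient who misses three consecutive weeks and then returns is unambiguous.

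The cost is protocol wording and some scheduling effort for patients who stopped attending. Full assessment also protects power (0.86 at 40 vs 40, against 0.77 at 28 vs 36, at the implied effect). The change is best made before post assessments begin, since missed ones cannot be recovered.

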### Randomization

Following eligibility and baseline assessment participants will be randomly assigned to either the intervention or control (TAU) group using an *ad hoc* Excel spreadsheet (69). We will stratify randomization by age, gender and years of education.

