### Length of the Study

The study will have a total length of 12 months, divided in the following phases.

Phase 1. Operators will be trained in evaluating neurocognitive functions, social cognition, functional capacity and real-life functioning. Phase 2. Different operators will be trained in SoCIAL program’s practice. Phase 3. Recruitment of patients and randomization (in both centers). Phase 4. Assessment of neurocognitive functions, social cognition, functional capacity and real life functioning for enrolled patients. Phase 5. Implementation of the interventions. Phase 6. Assessment of neurocognitive functions, social cognition, functional capacity and real life functioning in subjects at the end of the program for both groups (SoCIAL program vs. TAU). Phase 7. Final evaluation and data analysis.

The study’s timetable is shown in Table 1 and the flowchart in Figure 3.

**TABLE 1 T1:** Time schedule of the study.

	Enrollment	Pre-therapy assessment	Allocation	Intervention	Post-therapy assessment

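### Randomisation stratified only by age, gender and education does not secure the stated 20:20 split in each centre, and the described analysis names neither centre nor those factors

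*Protocol article*

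**What the plan says.** The Subjects section of the protocol article plans 80 patients, who "will be enrolled, 40 in each center". It then states the result of allocation: "Overall, 40 patients (20 for each center) will be assigned to SoCIAL and 40 (20 for each center) to the TAU".

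The Randomization section gives the mechanism. After baseline assessment, "participants will be randomly assigned to either the intervention or control (TAU) group using an" ad hoc spreadsheet, and "We will stratify randomization by age, gender and years of education". It mentions no centre factor, per-centre list, block size or cut-points. The Length of the Study section lists a phase described as "Recruitment of patients and randomization (in both centers", which says where randomisation takes place but not whether each centre has its own list.

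On analysis, the Data Analysis section says "Statistical analysis will be conducted by ANOVA for repeated measures", with type of intervention as the factor of interest. The Treatment as Usual section adds the number of therapy hours as a covariate. No analysis statement mentions centre, age, gender or education.

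**The concern.** The article states an exact split by arm within each centre, and it also states the factors on which allocation is stratified. Those factors do not include centre, so the second statement does not deliver the first.

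Centre is a natural factor to balance here. Usual care is whatever each patient already receives, it is delivered through two services in different cities, and outcomes and sessions depend on trained operators. If change from baseline differs between centres and the arms are unevenly spread over them, part of that difference enters an unadjusted treatment contrast.

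The factors that were chosen raise a second question. Two of the three (age and years of education) are continuous, and crossing several factors in 80 patients gives small cells. A third question is the model: factors used to balance the arms should also be in the analysis, otherwise the standard error does not reflect the balance that was achieved.

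**Working it through.** **Inputs.** 80 patients, 40 per centre, 1:1, 20 per arm per centre (Subjects). Factors: age, gender, education (Randomization). Required total 68 at power 0.8 and significance level 0.05 (Data Analysis). Assumed, because the article does not say: two levels per factor, blocks of 2 or 4, a two-sided test.

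**1. The plan's own figure.** The total of 68 cannot be reproduced, because no effect size is given. Solving backwards with 34 per arm: d = (1.960 + 0.842) × √(2/34) = 0.68. This value is used only in step 5; the figure of 68 is not in dispute here.

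**2. Centre ignored, 40:40 forced overall.** The number X of SoCIAL patients in one centre is hypergeometric (80 patients, 40 SoCIAL, 40 drawn).
- P(X = 20) = C(40,20)² / C(80,40) = 0.177. With the total fixed, this is also the chance that both centres are 20:20.
- P(17:23 or worse, either direction) = P(|X − 20| ≥ 3) = 0.263.
- Central 95% range of X: 16 to 24.

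**3. Closer to the stated scheme.** Permuted blocks in 2 × 2 × 2 = 8 strata pooled over centres, 20,000 simulated trials per setting.
- Both centres exactly 20:20: about 7% (blocks of 2) or 5% (blocks of 4).
- 17:23 or worse in a given centre: about 27% or 28%.
- 95% range of X: about 15 to 25.

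The three named factors therefore do not balance centre indirectly.

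**4. What an imbalance costs.** Take 24:16 in one centre and 16:24 in the other.
- Centre in the model: variance ratio = (20 × 20)/(24 × 16) = 400/384 = 1.04, about 4% more variance.
- Centre not in the model: 24/40 − 16/40 = 0.20 of any between-centre difference in the outcome analysed passes into the treatment contrast. In the group-by-time test that outcome is change, so a centre difference that is constant over time contributes nothing.

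**5. What omitting balanced factors costs.** Let them explain a share R² of the variance of the analysed outcome. The true two-sided error rate is then 2 × [1 − Φ(1.96/√(1 − R²))]. Power is for 40 per arm at d = 0.68.

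| R² (assumed) | True error rate | Power, factors omitted | Power, factors included |
|---|---|---|---|
| 0.05 | 0.044 | 0.87 | 0.88 |
| 0.10 | 0.039 | 0.87 | 0.89 |
| 0.30 | 0.019 | 0.90 | 0.95 |

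**6. What a remedy delivers.**
- Blocks of 2 or 4 within centre alone: exactly 20:20 in both centres in every trial, provided each centre enrols 40.
- Centre added to the eight strata: 16 cells, 80/16 = 5 patients on average. Both centres are exactly 20:20 in only about 15% (blocks of 2) or 9% (blocks of 4) of trials, but 17:23 or worse falls to about 1% or 5%, and the 95% range narrows to 18 to 22.

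**The case against.** The strongest reply is that the Subjects section already makes the split part of the design, and that randomisation takes place in both centres. Each centre may well allocate its own 40 patients, with age, gender and education as further factors. That reading is possible and cannot be excluded. It means the split is not secured by the text, not that it will fail. If separate lists are intended, the Randomization section is incomplete and still has to be reconciled with Subjects.

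A reader might go further and quote the figures for simple allocation: a 12.5% chance of 20:20 and a 43% chance of 17:23 or worse in a given centre. Those assume unstratified allocation with no fixed total, which the article does not describe. Steps 2 and 3 are the relevant cases, and even they depend on centre being ignored.

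On the analysis, the reply is that a condensed article need not list every covariate and a fuller plan may add them. That stands in part: the article does not mention these terms, which is weaker than excluding them. It does, however, fix a model and name one covariate. Therapy hours may absorb some local difference in usual care, but they do not stand in for centre or for the randomisation factors.

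It is also fair that number of levels, cut-points and block sizes are details an article may leave out. The eight-stratum figures are therefore illustrative.

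**Conclusion.** The point holds as a gap between two stated parts of the design, with modest consequences. As described, the method leaves roughly a one in four chance of 17:23 or worse in a centre (26% with the overall total forced, about 27% to 28% with blocks in eight assumed strata). This rests on centre being ignored in allocation.

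A reader might infer that arm and centre will be confounded, or that the standard errors are seriously wrong. The documents do not support either. Constant differences between centres, ages, genders or education levels cancel in the group-by-time comparison. Bias or lost precision arises only if these factors predict change, and nothing in the article shows how strongly they do. With centre in the model, a 24:16 and 16:24 split costs about 4% in variance. Leaving out balanced factors makes the test conservative: at an assumed 10% of variance explained, the error rate is 0.039 and power is 0.87 rather than 0.89, using the back-solved effect of 0.68. The sample size of 68 does not depend on this point. The change is worth making because it costs little and secures a feature the article itself states.

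**What to change.** 1. Reconcile the Subjects and Randomization sections: name centre as a stratification factor and state that each centre has its own blocked list. If that is already the practice, one sentence is enough.
2. Choose how exact the split must be. Blocking by centre alone secures 20:20 if each centre enrols 40. Centre × gender blocks, or minimisation that includes centre, keep the split close but do not guarantee it.
3. Handle age and years of education by minimisation or as continuous covariates, not by crossing them into many small strata.
4. Include centre and every factor used in randomisation in the primary model, each with its interaction with time. In a pre/post repeated-measures ANOVA a main effect alone does not alter the group-by-time test.

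Cost: if the list is not already by centre, it is rebuilt before the first patient. A few degrees of freedom are spent. Where age and education enter only as covariates, they are balanced by adjustment and not by strata.
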